### Identification of at-risk patients

At-risk patients are those patients for whom distance to the clinic is greater than the average distance and who are diagnosed with a chronic illness including diabetes, obesity, hypertension, or hyperlipidemia. This was chosen so that feasibility and acceptability could be assessed in this difficult population and so that one of the monitoring devices used will monitor one of the diagnosed chronic illnesses. Our previous pilot studies using the EMR of the rural healthcare clinic where the intervention will take place have identified that mean travel distance to this clinic for patients is 21 miles. The clinic has more than 28,000 patient encounters annually and provided chronic illness care to 1,734 patients in 2013. Of the patients with chronic illnesses, 637 patients live greater than 21 miles from the clinic. Given these parameters, the identification of 30 participants is feasible and will be done through the recommendations of Nurse Practitioners in the clinic and inclusion criteria.

### Potential participants

Inclusion criteria include being an adult age 18–64 with a diagnosis of a chronic illness and receiving care at the free clinic. The free clinic where the trial takes place does not accept patients with Medicaid. Hence, those over the age of 65 do not attend this particular clinic. Study participants will be of both genders. Exclusion will include participants who do not speak or read English at a 3rd grade reading level, and those with dementia or psychosis that would prevent on-going education and communication.

### Demographics

Demographics will be collected so that descriptive reports of the sample can be reported. The following demographics will be collected: Age, Gender, Ethnicity, Marital Status, Education, Income, Employment status, co-morbidities, duration of chronic illness, number of people in household, distance from clinic.

### Feasibility and acceptability

The use of the developed technology to deliver the intervention and to collect and store data will be evaluated in four ways. We will assess the ability of participants to use the developed technology to receive and transmit health information by: (1) reviewing the presence or absence of data in the database from each participant, (2) assessing the electronic activity logs and error messages for each participant, (3) assessing the electronic activity logs and error messages for each provider (4) analyzing the electronic activity logs of each application for number of times each application was used as well as common errors. Lastly, we will assess the acceptability of the technology with post intervention electronic patient and provider satisfaction questionnaires.

### Patient–provider communication and satisfaction

Participants will be provided questionnaires to assess communication based on 5-point Likert scale. We will evaluate ease and convenience of communication, promptness of replies, quality and amount of information, and quality of care. In addition, participants will assess their satisfaction with the overall system. The provider’s communication and satisfaction will measure the amount of time to review electronic logs and reply to electronic messages, their promptness in responding to messages, volume of messages, convenience of the system, quality of the information, and satisfaction with the electronic communication. All communication requiring interaction between the patient and health care provider will be stored in an activity log. The activity log will be analyzed for frequencies of all patient-provider communication.

### Adherence to treatment

The number of blood glucose, blood pressure and weight measurements uploaded to the database will be compared to the number of provider-requested measurements. Additionally, it is expected that trending improvement in blood glucose, blood pressure, and weight will be seen.

### Self-management ability

We will measure self-management ability with the American Association of Diabetes Educators (AADE) Behavior Score Dashboard (BSD). This tool is free to use for practicing diabetes educators and is already used by the clinic. It is designed to use with patients to examine all areas of self-management. The assessment includes 21 questions related to behaviors such as healthy eating, being active, monitoring, and taking medications. This tool will be used to provide a patient specific framework for individualized diabetes education. Additionally, we will use the tool as a means of measuring both participant progress and mI SMART outcomes. This tool is recommended by the AADE. Face validity of the instrument was established by an expert panel put together by the AADE. The expert panel found the BSD to be consistent across questions, clear and readable at lower literacy levels. The expert panel also determined that the questions were well constructed and understandable (Tomky 2011). However, psychometric measurements of validity and reliability have not yet been published. Participants will take this survey electronically prior to intervention and after 12 weeks of care.

### Quality of life and functional ability

Quality of life, loneliness, and depression will be measured to assess the base line patient perceived quality of life, loneliness and depression. Post intervention measures will be used to assess the differences in these measures after this intensive support intervention.

*Quality of life* The Medical Outcomes Trust Short Form-36 Health Survey versions 2.0 (SF-36v2), will be used to will be measure quality of life. The SF-36v2 is a 36-item questionnaire that reflects eight general health concepts including physical functioning (10-item), role-physical functioning (4-item), bodily pain (2-item), mental health (5-item), role-emotional functioning (3-item), social functioning (2-item), vitality (4-item), and general health (5-item). Each item is coded with a numerical value, summed, and transformed to a scale ranged from 0 to 100 (the higher score, the better state of health). Reliability and validity of the SF-36 is supported by many studies. The instrument is easy to administer in 5–10 min. Participants will take this survey prior to intervention and after 12 weeks of care (McHorney et al. 1993). *Loneliness* The 20 item University of California, Los Angeles (UCLA) Loneliness Scale (version 3) will be used to assess loneliness. It reflects a conceptualization of loneliness as a complex phenomenon with both emotional and social components. The current version, version 3, appeared in 1996 and includes 11 positively worded and nine negatively worded items. All items can be answered using a Likert scale, with potential answers of “never,” “rarely,” “sometimes,” and “often”; each answer is assigned a point value ranging from 1 (never) to 4 (often). Possible total scores range from 20 to 80, with 20 indicating no loneliness and higher scores indicating greater loneliness. Scores over 40 are generally considered to indicate loneliness. The scale has high internal consistency (a Cronbach α of 0.89–0.94)and positive test retest reliability (r = 0.73) (Russell and Cutrona 1980). Participants will take this survey prior to intervention and after 12 weeks of care.

*Depression* The Patient Health Questionnaire (PHQ-9) is a 9 item multipurpose instrument for screening, diagnosing, monitoring, and measuring the severity of depression. The tool rates the frequency of depressive symptoms as well as the presence and duration of suicidal ideation. The PHQ-9 can be completed in a few minutes and can be administered repeatedly to assess for improvement or worsening of depression. The tool had a sensitivity of 88 % and a specificity of 88 % for major depression. Scores of 5, 10, 15, and 20 represent mild moderate, moderately sever and severe depression (Kroenke et al. 2001). Participants will take this survey prior to intervention and after 12 weeks of care.

*Blood glucose, blood pressure, and weight* The physical measures of body weight, blood glucose and blood pressure will be measured because these are commonly collected at clinic visits as measures of chronic illness control. Participants will have body weight, blood pressure, and blood glucose obtained upon enrollment into the study by the blue-tooth enabled scales, blood pressure monitors, and glucometers. These Bluetooth-enabled devices will send the readings directly to the study database. Participants will continue to perform these physical measures and have these measures recorded at home with provided equipment as often as directed by their primary care provider. The mI SMART system will also provide automated prompts to obtain readings along with automated immediate feedback for readings within normal limits and timely feedback from study nurses with appropriate referral for abnormal readings. Goals for self-monitoring are set by the primary care provider, are patient specific, and are displayed as green for normal results, yellow for slightly low or high readings and red for critical values.

### Analysis of data

Data analyses will be facilitated by [name], the bio-statistician on our team, using SAS (Cary, NC) for Windows, version 9.3. For this feasibility and acceptability trial, we will be using a pre/post design. Techniques for assessing differences before and after the mI SMART intervention will depend on the type of outcome. For outcomes which are scaled, i.e., patient-provider satisfaction, the quasi-likelihood analysis will be used to determine if the intervention had an effect on the distribution of scores. For continuous outcomes, i.e., blood glucose, blood pressure, weight, the standard *t* test will be used to test differences in means before and after intervention. If the data are not normally distributed, the non-parametric Wilcoxon rank sum test will be used. For count measures, i.e., patient-provider communication, Poisson regression will be performed to assess the difference in mean counts before and after intervention. For measures that are percentages, i.e., for adherence to treatment measures (as patients will only measure themselves a certain percentage of the prescribed number) logistic regression will be performed to determine the difference pre and post intervention. Each of these analyses will be performed at a significance level of 0.05.

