### Sub aim 1b

To improve overall health status and the ability of patients to attend scheduled clinic visits in rural settings, a new approach to solving rural health disparities is needed. The objective for this Sub aim 1b is to evaluate the feasibility, acceptability, and outcomes of care using mI SMART. To attain the objective for this aim, we will test the feasibility and acceptability of mHealth care delivery through identification of at-risk patients and measure outcomes of care, including patient–provider communication, adherence to treatment, self-management ability, quality of life, blood glucose, blood pressure, and weight. We will give at participants an Android tablet, a Bluetooth enabled glucometer, blood pressure cuff, and scale along with a training session on how to use the devices. The replacement of broken or damaged equipment will be managed by the project coordinator and sent to participants via postal mail or patient pick-up at the clinic. We will pursue an approach of combined activity logging and questionnaires to evaluate provider communication, adherence to treatment, feasibility, and acceptability. We will use a pre/post design with no randomization or control group. Because of budgetary constraints, we will enroll 30 participants into the study. A larger randomized control trial is planned after analysis of the results of this study.

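### The fallback named for before/after glucose, blood pressure and weight is an independent-samples test (Wilcoxon rank sum), and the t test is not stated to be paired

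*Protocol article*

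**What the plan says.** Under Sub aim 1b the protocol article fixes the design: "We will use a pre/post design with no randomization or control group". The size is fixed there too: "Because of budgetary constraints, we will enroll 30 participants into the study". The section on quality of life and functional ability, which also covers the physical measures, sets the baseline: "Participants will have body weight, blood pressure, and blood glucose obtained upon enrollment into the study". The same people then keep measuring themselves at home with the supplied devices.

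Under Analysis of data the first-line test reads: "For continuous outcomes, i.e., blood glucose, blood pressure, weight, the standard" *t* "test will be used to test differences in means before and after intervention". The next sentence gives the alternative: "If the data are not normally distributed, the non-parametric Wilcoxon rank sum test will be used". The paragraph closes: "Each of these analyses will be performed at a significance level of 0.05".

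The article does not mention pairing, within-person differences or the signed-rank test anywhere.

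**The concern.** Each participant supplies a before value and an after value, so the two sets of readings are linked person by person. The rank sum test takes its null variance from two samples of unrelated people. No reading of a single-group pre/post design makes that assumption true. The paired counterpart is the signed-rank test, which is a different procedure.

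The t test wording leaves open whether it is the paired or the two-sample version. A reader who pairs it with its named fallback could well program the two-sample version. The normality condition is attached to the data in general, whereas for a paired analysis it matters for the differences.

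These tests carry some weight. The abstract hypothesizes improvement in glucose, blood pressure and weight, and the intervention section says the 12-week length was chosen so that such change could be detected. A larger randomized trial is planned once these results have been analysed. The sample is capped by budget, so precision lost in the analysis cannot be bought back by enrolling more people. A real change could be missed.

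**Working it through.** The article states no power, effect size or standard deviation, so there is no figure of its own to reproduce. The check is how an unpaired analysis of these data would behave.

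**Inputs from the article:** 30 participants, one group, before and after, significance level 0.05.

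**Assumptions:** two-sided tests, equal SDs before and after, 30 complete pairs, bivariate normal values. The pre/post correlation rho is not given for glucose, blood pressure or weight, so a range is shown. The only retest figure in the article is 0.73, for the UCLA Loneliness Scale. It concerns a different kind of outcome and appears below only as an illustration.

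**Standard error of the mean change**, with SD the common standard deviation and n = 30:
- unpaired: SD × sqrt(2/n)
- paired: SD × sqrt(2(1 − rho)/n)
- ratio: 1/sqrt(1 − rho). For example, at rho = 0.5 it is 1/sqrt(0.5) = 1.41.

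**Change that gives the paired t test 80% power.** From the noncentral t distribution with 30 pairs this is 0.529 SDs of the differences. In units of SD it is 0.529 × sqrt(2(1 − rho)). For example, at rho = 0.7 it is 0.529 × sqrt(0.6) = 0.41.

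**Rejection rates** come from 20,000 simulated trials per setting (5,000 for the signed-rank test). The power columns use the change shown in the third column.

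| rho (assumed) | SE ratio | change (SD) | actual type I error, two-sample t / rank sum | power, two-sample t / rank sum | power, signed-rank |
|---|---|---|---|---|---|
| 0.3 | 1.20 | 0.626 | 0.018 / 0.018 | 69% / 66% | 77% |
| 0.5 | 1.41 | 0.529 | 0.006 / 0.006 | 54% / 50% | 79% |
| 0.6 | 1.58 | 0.473 | 0.003 / 0.004 | 41% / 38% | 78% |
| 0.7 | 1.83 | 0.410 | 0.001 / 0.001 | 25% / 23% | 78% |
| 0.73 | 1.93 | 0.389 | 0.0004 / 0.0003 | 20% / 19% | 78% |
| 0.8 | 2.24 | 0.335 | 0.0001 / 0.0001 | 8% / 8% | 79% |
| 0.9 | 3.16 | 0.237 | no rejections | below 1% / below 1% | 78% |

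Half of 80% is 40%, and the unpaired tests reach that level at rho of about 0.6.

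**Same comparison at a fixed change of 0.5 SD.** Power of the paired t test against the two-sample t test is 61% against 47% at rho 0.3, 75% against 47% at 0.5, 93% against 47% at 0.7, and 99% against 46% at 0.8. The unpaired test gains almost nothing from the correlation.

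**Sanity checks.** At rho = 0 all four tests reject a true null at 4.6% to 4.9%, as they should. A closed-form approximation for two independent groups of 30 and a change of 0.5 SD gives 49% power, against 48% simulated.

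**The case against.** The strongest reply has four parts.

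- **The t test may well be paired.** The analysis section opens by restating the pre/post design, and testing a difference in means before and after fits a paired test equally well. The rank sum name could be a slip for signed-rank, and an analysis plan that is not shown may settle the matter. This stands. A reader might infer from the fallback that the t test is certainly two-sample, but the article does not say so. For the t test the point is an ambiguity. For the fallback it is a stated error and not an omission, and it takes effect only if the data are judged non-normal.
- **The power loss rests on an assumed correlation.** This also stands. A reader might conclude that most of the power is lost, but at rho 0.3 to 0.5 the unpaired tests keep 50% to 69% out of 80%.
- **The next trial's planning figures are not spoiled.** It is tempting to say that the SD of change handed to the randomized trial would be wrong. That SD is computed from the within-person differences and does not depend on which test is run. The analysis section also promises no confidence intervals, so none can be called too wide.
- **The stakes are limited.** The main aim is feasibility and acceptability, the sample is set by budget, no power is claimed, and the error is conservative when the correlation is positive. This lowers the severity. It does not make the named test right, since the article tests these outcomes at 0.05 and the test would not run at that level.

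**Conclusion.** The Wilcoxon rank sum test is wrong as written for before/after values from the same participants, and the t test needs the word paired to be unambiguous. If the unpaired versions are used and the correlation is positive, the standard error of the mean change is too large by 1/sqrt(1 − rho). The actual type I error falls to about 1.8% at rho 0.3 and 0.6% at rho 0.5, and power drops as tabulated. The sizes rest on assumed correlations, normal data, equal SDs, two-sided testing and no dropout. The direction needs only a positive correlation, which is to be expected for repeated readings in the same people.

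This should be fixed before analysis. It does not threaten the feasibility aim and does not create false claims of benefit; the risk is that a real change goes undetected.

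**What to change.** Replace the two sentences on continuous outcomes with wording such as: paired t test on each participant's after-minus-before difference; if these differences are clearly non-normal, the Wilcoxon signed-rank test. State that normality is judged on the differences and not on the separate before and after values.

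The cost is a few words. No new data, visits or participants are needed, because the readings are already linked by participant. Where the differences are close to normal, choosing the signed-rank test costs little: 77% to 79% power where the paired t test has 80%.

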### The intervention

The creation of mI SMART is being guided by the model for developing complex nursing interventions (Corry et al. 2013). The multi-dimension technology intervention is designed to replicate what is accomplished through standard in-person outpatient primary care visits. The distance intervention will last for 12 weeks. Twelve weeks were chosen so that a change in biophysical outcomes could be detected and so that preliminary data could be analyzed in order to begin developing the subsequent application toward the end of the 2nd year of this grant. The participants will receive education related to self-management of their chronic illness via the developed video teleconferencing system. The curriculum for the education was developed by JM and TW and adapted from the National Standards for Diabetes Self-Management Education and Support (Haas et al. 2013) and will be delivered by a team consisting of a Nurse Practitioner, a Pharmacist (PharmD) or a Board Certified in Advanced Diabetes Management professional. The curriculum has been tested in previous interventions in this clinic and found to be effective. Using the developed video teleconferencing system, the patients will be provided tailored education about blood glucose monitoring, medication, nutrition, exercise, foot care, heart disease, complications of chronic illnesses, and behavior change. A Nurse Practitioner will perform a limited physical exam, a through health history, medication adjustments, appropriate referrals and a cardiovascular risk factor assessment with treatment as indicated for all abnormal results via the developed video teleconferencing system. A Registered Nurse will review and provide feedback and appropriate referral for finger stick logs, blood pressure logs and weights via the developed secure messaging system.

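### A normality check can replace the planned test of mean change in glucose, blood pressure and weight with a rank test, so what is tested is not fixed in advance

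*Protocol article*

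**What the plan says.** The Analysis of data section of the protocol article covers blood glucose, blood pressure and weight together. It names the question: the standard t "test will be used to test differences in means before and after intervention". The next sentence gives the exception: "If the data are not normally distributed, the non-parametric Wilcoxon rank sum test will be used". The section closes with "Each of these analyses will be performed at a significance level of 0.05".

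The design is described under Sub aim 1b: "We will use a pre/post design with no randomization or control group". The size is set there too: "Because of budgetary constraints, we will enroll 30 participants into the study". Under Identification of at-risk patients, eligible people are those "diagnosed with a chronic illness including diabetes, obesity, hypertension, or hyperlipidemia", so the sample may contain people with and without diabetes. The article does not give the expected share with diabetes, a glucose distribution or a standard deviation. It does not say how normality is judged, or whether raw readings or within-person changes are judged.

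**The concern.** The two sentences answer different questions. The t test concerns the mean. A rank test concerns the ordering of values, and its result translates into a statement about means only under further assumptions, such as every participant shifting by the same amount. That is hard to presume when people with and without diabetes are pooled.

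Because the observed distribution picks the test, the target of each analysis is unknown until the data are in. Glucose could be analysed by ranks while blood pressure and weight are analysed by means, all under one stated aim. The results would then not be comparable across outcomes, and a significant rank result could be reported as a change in mean that was never tested.

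This is a rule the article states, not a detail it leaves to an analysis plan. An analysis plan could supply a criterion for normality, but any criterion would still swap one target for another. The absence of a criterion is therefore not the complaint.

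**Working it through.** **Inputs from the article.** 30 participants; one group measured before and after; significance level 0.05 (taken as two-sided; the article does not say). There is no power or sample-size calculation to reproduce, because 30 is a budget figure.

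**Inputs assumed.** Everything about glucose, so ranges are shown. The normality check is taken to be Shapiro-Wilk at 5%.

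**Step 1: how often the switch would occur for glucose.** Main model: glucose in people with diabetes is lognormal with mean/SD 150/30, 150/45 or 180/60 mg/dL; in others it is normal 95/10; the before-after correlation is 0.5 or 0.7; 3,000 simulated studies of 30 per setting.

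| Share with diabetes | Raw baseline values fail | Within-person changes fail |
|---|---|---|
| 10-50% | 82-100% | 38-93% |
| 70% | 30-80% | 21-48% |
| 90% | 10-44% | 10-22% |
| 100% | 19-42% | 8-15% |

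Overall the range is about 8% to 100%. With 24 completers the rates are equal or lower. A second model with normal glucose in both groups (180, SD 50 and 100, SD 12) shows the same dependence. Raw values fail in about 100% of studies with 12 of 30 diabetic, 59-60% with 20, 15% with 24 and 5% with 27; changes fail in 89%, 41%, 16% and 7%. An outcome that is truly normal fails in about 5% of samples, or 8-10% if before and after values are each checked.

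**Step 2: does the switch inflate type I error?** With no mean change in any participant group and mixed or skewed glucose, the two-stage rule (check the changes, then paired t or signed-rank) rejects in 0.041 to 0.057 of studies. The paired t test alone rejects in 0.042 to 0.054, so the check is not needed to hold the level. Steps 2 to 4 use paired forms of both tests, to separate this point from the choice of an unpaired test.

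**Step 3: do the two tests have the same target?** Take two cases built so that the overall mean change is zero:
- 40% change by -7.5 (SD 30) and 60% by +5 (SD 8): 0.4 x (-7.5) + 0.6 x 5 = -3 + 3 = 0. Paired t rejects in 4.0%, signed-rank in 10.0%.
- 30% change by -14 (SD 30) and 70% by +6 (SD 8): 0.3 x (-14) + 0.7 x 6 = -4.2 + 4.2 = 0. Paired t rejects in 3.7%, signed-rank in 14.5%.

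These cases are artificial. They show only that the rank test can respond when the mean has not moved.

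**Step 4: which test has more power?** 12 of 30 diabetic; SD of change 40 in them and 10 in the others.

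| Change, diabetes / others (mg/dL) | Mean change | Paired t | Signed-rank |
|---|---|---|---|
| -30 / 0 | 0.4 x (-30) = -12 | 59-61% | 41-42% |
| -30 / -3 | -12 - 1.8 = -13.8 | 77% | 73% |
| -30 / -5 | -12 - 3 = -15 | 83-85% | 86% |
| -15 / -5 | -6 - 3 = -9 | 44% | 55% |

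Ranges come from repeated runs of the same scenario. The ranking reverses once people without diabetes also improve a little.

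**The case against.** A fallback to a rank test is conventional. Where the distribution of changes is symmetric, the mean and the rank target share the same centre, so the switch costs little in interpretation. This is also a small uncontrolled feasibility study, and choosing a rank test for the p-value does not stop anyone reporting a mean change. All of this bears on the priority, but the stated rule still lets the data choose the question.

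Four stronger readings are tempting, and the article does not support them.

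- *The check will almost always fail for glucose.* This needs a diabetes share and a distribution that the article does not give. A sample made up mostly of people with diabetes is quite possible: the curriculum derives from diabetes education standards, the self-management tool is a diabetes tool, and everyone receives a glucometer. In such a sample failure is often the less likely result. Nothing suggests a high failure rate for blood pressure or weight.
- *The check is applied to the wrong quantity.* The sentence refers only to the data. It does not say raw values rather than changes.
- *A real effect is more easily missed, or false positives rise.* Step 4 shows the power ranking depends on whether people without diabetes also change; the intervention offers nutrition, exercise and medication support to all participants, so no change in them is not a natural default. Step 2 shows the level is held when nobody's mean changes.
- *The next application needs the mean change.* The intervention section says only that "preliminary data could be analyzed in order to begin developing the subsequent application"; it does not say which summary is required.

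**Conclusion.** The point holds in a limited form. The article states a question about means and a rule that can replace it with a question about ranks after the data are seen, possibly for some outcomes and not others. That follows from the text and needs no assumption.

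How often it would happen cannot be fixed from the article. For glucose it is plausible, and likely (82-100% in the main model) if raw values are checked and 10-50% of participants have diabetes. Across the main model's scenarios the range is roughly 8% to 100%. These figures rest on assumed glucose distributions and an assumed Shapiro-Wilk check.

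Priority is low to moderate. A separate defect in the same sentence is numerically larger: the rank sum test treats before and after values as independent samples. With normal data and 30 participants, its type I error falls to 0.010 at a correlation of 0.5 and 0.001 at 0.7. In the first scenario of Step 4 its power is about 1%, against 61% for the paired t test. Replacing it with a signed-rank test would cure that but leave the present point untouched.

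**What to change.** Delete the normality trigger. For glucose, systolic and diastolic pressure and weight, state in advance one analysis: the mean within-person change with its 95% confidence interval from a paired t analysis, whatever the distribution looks like, with a bootstrap interval as a check on the effect of skewness. Report a signed-rank test on the changes as a supporting analysis only, and do not describe it as a test of means.

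This changes one or two sentences in the Analysis of data section and requires no new data. It also removes the unpaired fallback. The price is that a mean is more sensitive to an extreme value than a rank statistic; the bootstrap interval and the supporting signed-rank test would help to show when that matters.
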